#### Smoking status questionnaire

This surveys tobacco use, use of other tobacco products, and nicotine replacement medications. The questionnaire also collects data on the use of other tobacco products and nicotine replacement medications as determined by the participant's time point in the protocol (e.g., based upon the date the participant quits smoking) [83].

#### Stages of change: physical activity

The Stages of Change: Physical Activity is a 1-item measure of the five stages of change in physical activity [89].

### Other measures

#### Brief Wisconsin Inventory of Dependence Motives

This questionnaire yields an overall dependence score as well as subscale scores for other critical dimensions of tobacco dependence (affiliative attachment, automaticity, loss of control, cognitive enhancement, craving, cue exposure/associative processes, social/environmental goads, taste, tolerance, weight control, and affective enhancement). The overall and subscale scores have high internal consistencies and predict abstinence [90].

*Demographics Questionnaire* collects data on age, race, ethnicity, education, income, preferred language, and generations in the U.S.

#### Medical history

Participants will be asked to provide a detail medical history including heart disease, asthma/lung disease, high blood pressure, diabetes, high cholesterol, thyroid problems, and kidney disease.

#### Medication worksheet

Participants will be asked to provide a detail list of medications and their dosage that they take daily.

#### Short assessment of health literacy for Spanish adults (SAHLSA)

The SAHLSA will be used to assess Spanish language health literacy. Participants are presented with a list of 50 common medical terms. Each word is presented with a synonym and a distracter word. The participant is instructed to pronounce each word and identify the synonym. A score of 38 is indicative of at least marginal health literacy, and higher scores indicate greater health literacy [75].

### Pharmacotherapy

All study participants will have access to free nicotine patch therapy when they are ready to make a quit attempt. The provision of patch therapy or other cessation medication is the recommended standard of care. As such, it is arguably an ethical obligation to provide all participants with access to patch therapy. Study participants receive nicotine patch therapy because the patch is currently recognized as a frontline therapy [22], and compared to non-nicotine medications such as bupropion or varenicline, the patch is safer, better tolerated, and available over the counter. Participants who decide to make a quit attempt will request patches by contacting project staff. Patches and instructions for their use will be distributed either via a visit to MD Anderson or via the mail. Patch therapy for participants who smoke >10 cigarettes/day will consist of 4 weeks of 21 mg patches, 1 week of 14 mg patches, and 1 week of 7 mg patches. Patch therapy for participants who smoke 6–10 cigarettes/day will consist of 4 weeks of 14 mg patches and 2 weeks of 7 mg patches. Patch therapy for participants who smoke 1–5 cigarettes/day will consist of 6 weeks of 7 mg patches. A reduction in dosage or cessation of the patch regimen will be implemented for any participants who report signs of being on too high of a dose, although this is typically not necessary for participants because blood nicotine levels are usually far lower on the patch than while smoking [91]. In sum, all participants, regardless of treatment group assignment, will have the same access to nicotine patch therapy. We will carefully track pharmacotherapy use at all follow-up assessments.

### Participant compensation and retention

To compensate for the time and inconvenience associated with participation, participants will be reimbursed $25 for each of the 4 assessments (i.e., up to a total of $100). Focus group participants will receive a gift card worth $50. Pilot study participants will receive a $25 gift card at each visit (Day 1 and Month 3), for a total of up to $50 in gift cards. Participants will not receive compensation for the counseling calls. Other procedures to reduce attrition include: 1) mailing postcard reminders and calling to remind participants of upcoming visits; 2) maintaining communication with participants throughout the study via birthday cards, holiday cards, etc. (each mailing includes a stamped address update postcard to update contact information); 3) having research staff member available during daytimes, evenings, and weekends to conduct study visits; 4) requiring that in addition to a functional phone number (necessary for counseling calls), participants have a home address so that they can be contacted by mail if necessary; and 5) obtaining names, addresses, and phone numbers of up to three collaterals (i.e., relatives/friends) who can provide information on participants’ whereabouts during the study (permission to contact the collaterals will be obtained from participants).

### Data analysis

Primary outcomes used to evaluate the efficacy of the MAPS intervention (Aim 1) are smoking status, servings of fruits and vegetables, and both self-reported and objectively measured physical activity assessed at the 6, 12, and 18 months. Because the primary outcomes and mechanisms include repeated measurements that are correlated within subjects, the data analytic approach utilizes generalized linear mixed model regression GLMM; [92,93]. Model diagnostics will be used to determine and address the form of the covariances, transformations, collinearity, and influential observations. GLMM parameter tests will be conducted using Wald statistics, and will be adjusted for multiple comparisons where appropriate. Adjustments for multiple comparisons will be made according to the method of Westfall and Young [94]. In this approach, the correlations among the dependent variables are used to adjust the critical values of the individual tests to ensure that the probability of a Type I error across a set of tests does not exceed the chosen alpha level. This approach has the advantage of maintaining the chosen Type I error rates while at the same time providing a less conservative adjustment than Bonferonni-type procedures.

#### Aim 1

Evaluate the efficacy of a MAPS approach to promoting and facilitating reduction of behavioral risk factors for cancer among high-risk Mexican-origin individuals (overweight/obese smokers). Relative to HE, MAPS is hypothesized to result in positive changes in each of the primary smoking, diet, and physical activity outcomes.

GLMM will be utilized in analyzing the effects of MAPS on the primary outcomes across the 6, 12, and 18-month time points. For the dichotomous outcome, we will assume a logit link and binomial variance function for the GLMM, and parameterize them with blocking on individual nested within treatment condition. Treatment and time will be included, as well as their interaction, with adjustment for relevant covariates as necessary. Time will be treated as a categorical variable. These models test for the main effects of treatment and time, and whether the treatment effect varies over time. For the continuous outcomes, the GLMM analysis will be replaced by linear mixed model (LMM) analysis (i.e., a special case of GLMM in which each outcome variable is continuous).

#### Aim 2

Assess the effects of MAPS on hypothesized treatment mechanisms (e.g., motivation, agency/self-efficacy, stress/affect) and the role of those mechanisms in mediating the effect of MAPS on outcomes.

To assess MAPS effects on treatment mechanisms, analyses largely analogous to the GLMM and LMM analyses described for Aim 1 will be conducted. Mediation will be indicated if: (a) there is a significant MAPS effect on the mechanism, and (b) the mechanism significantly predicts the outcome when adjusting for treatment. To formally test for the mediation effect, we will follow appropriate methods described by MacKinnon [95]. In particular, we will use a product-of-coefficients approach in which the indirect (mediation) effect is defined as the product of the coefficient of the intervention condition in the regression of the mechanism (*a* path) and the coefficient of the mechanism in the regression of the outcome variable controlling for intervention condition (*b* path), with appropriate coefficient standardization from *b* path, when the outcome is binary [95]. This approach is applicable for both continuous and binary outcomes (e.g., smoking status, servings of fruits and vegetables, and both self-reported and objectively measured physical activity), with and without repeated measurements. We will use a bootstrapping approach to computing confidence intervals of the indirect effects. Multiple mediator models will be fit to assess simultaneous mediation effects by multiple mechanisms. In addition to the tests for indirect effects, we will also calculate proportion mediated effects and standard errors in both the simple and multiple mediator models.

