### Study design

The current study is a two-group randomized controlled trial designed to test the efficacy of MAPS versus HE for multiple cancer risk behaviors among Spanish-speaking Mexican-origin smokers. Figure 1 depicts the study flow. Potential participants will call a phone number dedicated to study recruitment. They will undergo an initial eligibility screening (including BMI and smoking status eligibility based on self-report). Those who pass the initial screening and choose to participate will be scheduled to attend an in-person visit at the study site. Additional screening will take place, including objective verification of height, weight, and smoking status. Participants will also be screened for health literacy. After completing additional screening, those who choose to participate will complete the baseline assessment and the first of three HE sessions. After completing the first HE session, participants will be randomly assigned to HE or MAPS.

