**Figure 1 F1:**
[figure not shown]
Study flow.

Randomization will occur using a form of adaptive randomization called minimization [77,78]. Compared to techniques such as stratification, minimization results in better group balance on participant characteristics. Minimization also provides for balanced treatment groups throughout the randomization process. Randomization will be balanced on gender, age, immigrant status, cigarettes per day, and BMI.

Individuals randomized to the MAPS condition will schedule their first counseling call during the baseline visit, and subsequently receive up to 18 counseling calls over an 18-month period. Outcome assessments will occur at baseline, 6 months, 12 months, and 18 months. Also after completing the assessment and randomization procedures, the 6-month follow-up visit will be scheduled for all participants. Research staff conducting the outcome assessments will be blinded to participants’ treatment conditions.

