##### Accelerometer

Participants will wear a small blinded accelerometer (i.e., participant cannot see values) over 7 days to assess physical activity. Accelerometers will be distributed at each assessment visit and will be returned via mail.

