### Power

All power analyses assume a significance level of 0.05 and a two-sided test and accounts for a potential 20% attrition at all time points (N = 320; 160/group). Three of the outcomes are continuous (servings of fruits and vegetables, METS of physical activity, accelerometer assessed activity). One outcome (smoking status) is dichotomous. Power is expected to be greater for intent-to-treat analyses than the power reported here, which represents completers only analyses. This is because the total number of cases for intent-to-treat analyses will be 400, versus 320 for the completers only analyses. For intent-to-treat analyses, those lost to follow up will be coded as not abstinent.

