#### Continuous outcomes

Because treatment outcomes are measured at 6, 12, and 18 months, treatment effects may not be consistent across time points. In the case of a constant treatment effect across time, the detectable difference depends on the intraclass correlation coefficient (ICC) between measurements taken from a given participant. Since 160 participants per arm are assumed after attrition, and there are 3 measurements per participant, the effective sample size (ESS) per arm is 3*160/VIF, where VIF is the variance inflation factor 1 + (p-1)*ICC. In this formula, p is the average number of observations per participant. Table 1 shows the minimal detectable constant treatment effect under a range of values for the ICC when testing at a power of 80%. The detectable differences are given in terms of the standard deviation of the error term of the model. Thus, if the ICC is 0.3, the current study has 80% power to detect a shift of 0.229 standard deviations between the treatment arms, a small effect size per Cohen [104]. Power calculations displayed in Table 1 assume approximately consistent effects of treatment across measurements. However, correlations between more distal time points are generally lower than more proximal time points. Thus, calculations presented in Table 1 represent a worst-case scenario. We further computed power for detecting an average intervention difference of 0.3 when the effect varies across time points, specifically, with a shift of 0.1 at 6 months, 0.3 at 12 months, and 0.5 at 18 months. A Geisser-Greenhouse Corrected F Test was used for testing the intervention effect. The estimated power for detecting the treatment effect was 99%, 96%, and 91% for ICC values of 0.1, 0.3, and 0.5, respectively. It is important to note that the presented case of a 0.1, 0.3, and 0.5 increasing difference across time points produces exactly the same power as that of a 0.5, 0.3, and 0.1 decreasing difference across those time points.

**Table 1 T1:** Minimal detectable difference with constant effect

**ICC**	**VIF**	**ESS**	**Detectable difference**
0.0	1.0	480	0.181
0.1	1.2	400	0.198
0.3	1.6	300	0.229
0.5	2.0	240	0.256
1.0	3.0	160	0.314

Note: ICC = intraclass correlation coefficient; VIF = Variance Inflation Factor; ESS = Estimated Sample Size.

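### The Aim 1 models for the continuous outcomes do not commit to the collected baseline value, which costs precision; the accelerometer needs a different covariate because its week-0 record follows randomisation

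*Protocol article*

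**What the plan says.** Under Aim 1 in the Data analysis section, the primary outcomes are analysed at the three follow-ups, with time categorical and linear mixed models for the continuous outcomes. On model terms: "Treatment and time will be included, as well as their interaction, with adjustment for relevant covariates as necessary". No covariate is named there.

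Baseline values exist. Below Figure 1 the Study design section says: "Outcome assessments will occur at baseline, 6 months, 12 months, and 18 months". The Instruments section makes the procedures the same at all four visits, apart from some demographic items.

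Minimisation balances gender, age, immigrant status, cigarettes per day and BMI. It does not use baseline diet or activity.

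On the order of events at the first visit, the Study design section puts the baseline assessment first, then the first HE session, and then: "After completing the first HE session, participants will be randomly assigned to HE or MAPS". MAPS participants book their first counselling call at that same visit. On the accelerometer, which is worn for 7 days: "Accelerometers will be distributed at each assessment visit and will be returned via mail".

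The power calculation for continuous outcomes rests on the three follow-up measurements alone: "the effective sample size (ESS) per arm is 3*160/VIF, where VIF is the variance inflation factor 1 + (p-1)*ICC".

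**The concern.** A participant's starting level usually predicts the later level of the same behaviour. An analysis that leaves it out carries between-person variation that it could have removed for nothing. Making adjustment conditional, with no covariate named, also leaves the choice open until the data are in hand.

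The accelerometer raises a separate difficulty. An analyst who later decides in good faith to adjust every outcome for its baseline would, for this one, adjust for a week of activity recorded after allocation. If MAPS had already moved activity in that week, the adjustment would remove part of the effect under test.

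**Working it through.** **Inputs.** From the Power section: "All power analyses assume a significance level of 0.05 and a two-sided test"; 160 participants per arm after 20% attrition; 80% power for Table 1; three follow-ups; effects in SD units. The article does not give the correlation r between baseline and follow-up, so r is an assumption throughout.

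**Step 1: reproduce Table 1.** ESS per arm = 480/(1 + 2·ICC), and detectable difference = (1.960 + 0.842)·√(2/ESS).
- ICC 0.1: 2.802·√(2/400) = 0.198
- ICC 0.3: 2.802·√(2/300) = 0.229
- ICC 0.5: 2.802·√(2/240) = 0.256

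These match the table. The same ESS gives power of 98.9%, 95.7% and 90.8% for an average difference of 0.3 SD, against the stated 99%, 96% and 91%.

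**Step 2: add one baseline covariate.** With unit variances, the mean of three follow-ups has variance (1 + 2·ICC)/3 and covariance r with baseline. The share of variance removed is r²/[(1 + 2·ICC)/3] = 3r²/(1 + 2·ICC). The detectable difference is multiplied by √(1 − share).

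**Step 3: take r equal to the ICC.**

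| ICC = r | Share removed | Detectable difference (SD) | Power at 0.3 SD |
|---|---|---|---|
| 0.1 | 0.03/1.2 = 2.5% | 0.198 to 0.196 | 98.9% to 99.0% |
| 0.3 | 0.27/1.6 = 16.9% | 0.229 to 0.209 | 95.7% to 98.1% |
| 0.5 | 0.75/2.0 = 37.5% | 0.256 to 0.202 | 90.8% to 98.6% |

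At ICC 0.5 the ESS per arm goes from 240 to 240/0.625 = 384. Simulation with 4,000 trials per ICC gave reductions of 1.8%, 17.1% and 38.9%.

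**Step 4: let r differ from the ICC.** The Continuous outcomes section itself expects lower correlation between more distant visits.
- Follow-up ICC 0.5 with r = 0.2, 0.3, 0.4: 3r²/2 = 6%, 13.5%, 24%. The detectable difference becomes 0.248, 0.238 and 0.223 SD (0.2557 times √0.94, √0.865 and √0.76).
- First-order autoregressive decay with adjacent-visit correlation 0.5, 0.6, 0.7: 14%, 23%, 35%.

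**Step 5: the accelerometer.** Assessment, HE session and randomisation all fall within the baseline visit. The device is handed out at that visit, worn for 7 days and posted back, so the week-0 record follows allocation. IPAQ belongs to the assessment completed before the HE session, so baseline IPAQ precedes allocation. The formula in Step 2 needs the correlation between baseline IPAQ and later accelerometer activity. The article does not give it, so no gain is computed.

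If MAPS shifted week-0 activity by d and the covariate slope were b, adjusting for that record would remove b·d from the estimate. Purely as an illustration, d = 0.1 SD with b equal to the ICC would remove 0.03 SD at ICC 0.3 (0.03/0.229 = 13% of the detectable difference) and 0.05 SD at ICC 0.5 (0.05/0.256 = 20%). Neither d nor b is in the document.

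**The case against.** The best defence is that the plan does not exclude the baseline value. Its wording lets in relevant covariates, and the baseline outcome is an obvious one. A journal article also commonly leaves the covariate list to a full protocol or SAP, and neither is shown here. That stands against any claim that the baseline is left out of the analysis for good. It does not remove the point: the article does fix the visits and core terms, makes adjustment conditional, and bases its power on follow-ups alone, while a better specification is available from data already collected.

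Nor is the unadjusted analysis wrong. Under randomisation, the difference in follow-up means is unbiased and also estimates the between-arm difference in change. A reader might infer that chance imbalance in diet or activity biases the result, or that a hypothesis about change contradicts the model. Neither follows: chance imbalance is already reflected in the standard error. The stated power of 91% to 99% for a 0.3 SD average effect reproduces without any baseline term.

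On the accelerometer, no sentence says that the week-0 record will be a covariate or the base of a change score. The HE session and exercise kit reach both arms before allocation, and the first MAPS call is booked at the visit, not delivered there. All of this stands. The risk is conditional on a later choice, and its size is unknown.

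**Conclusion.** The point holds as a free gain in precision together with a safeguard for one outcome. For fruit/vegetable servings and IPAQ, committing to baseline would cut the variance of the average treatment effect by 2.5% to 37.5% over ICC 0.1 to 0.5, if baseline correlates with follow-up as the follow-ups do with each other. At follow-up ICC 0.5 with a weaker baseline correlation of 0.2 to 0.4, the saving is 6% to 24%.

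A reader might infer that the plan throws away 37% of the variance on three of the four primary outcomes. The document does not support that. The figure needs both ICC 0.5 and an equal baseline correlation, and it does not extend to the accelerometer, whose usable covariate is a different instrument.

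A reader might also infer that the accelerometer result will be biased. It will not be on this account unless the week-0 record is used for adjustment or change scores and MAPS has already affected activity in that week. What the document does establish is the order of events, and that is reason enough to rule out such use in advance.

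**What to change.** In the Aim 1 specification, state three things:
- The models for fruit/vegetable servings and IPAQ activity include the baseline value of the same measure as a fixed covariate.
- The accelerometer model includes baseline IPAQ, completed before randomisation.
- The week-0 accelerometer record is post-randomisation and is not used for adjustment or change scores.

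This takes one or two sentences, needs no further data or visits, and costs one model parameter per outcome. If a full protocol or SAP already names the baseline covariates, only the accelerometer entry needs checking against the order of events at the first visit.

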#### Instruments

The majority of the assessment instruments have been previously used and validated in Spanish, or are being tested in our current research. Assessment instruments measure outcomes or hypothesized mechanisms. We attempted to reduce the inconvenience associated with completing the assessment battery by providing financial compensation for participants’ time and by using the Questionnaire Design System (QDS), a computer-administered self-interview format. The error and time necessary to complete an assessment battery are substantially reduced by using QDS and particularly so among individuals with low literacy because the computer can read each item in Spanish to the participants. Assessment procedures will be identical at each of the four visits, with the exception that only a subset of the demographic measures will be administered at the 6, 12, and 18 month follow ups.

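### Aim 2 declares mediation from a mechanism-to-outcome path that adjusts only for treatment and sets no time order, so confounding or reverse causation can be reported as mediation

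*Protocol article*

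**What the plan says.** The Aim 2 text in Data analysis sets a two-part rule. Mediation is indicated if "there is a significant MAPS effect on the mechanism" and if "the mechanism significantly predicts the outcome when adjusting for treatment". The indirect effect is the product of the two coefficients, and the second (the b path) is "the coefficient of the mechanism in the regression of the outcome variable controlling for intervention condition". Bootstrap intervals, multiple-mediator models and the proportion mediated are also planned. The formal test is referred to a cited source: "To formally test for the mediation effect, we will follow appropriate methods described by".

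On timing, the section below Figure 1 says "Outcome assessments will occur at baseline, 6 months, 12 months, and 18 months". Instruments says "Assessment procedures will be identical at each of the four visits", apart from some demographic items. Mechanisms and outcomes therefore come from one battery, with a baseline value of each.

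On covariates, the Aim 1 models are fitted "with adjustment for relevant covariates as necessary". Aim 2 takes over those models for MAPS effects on mechanisms (the a path): "analyses largely analogous to the GLMM and LMM analyses described for Aim 1 will be conducted". No such clause is attached to the b path.

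**The concern.** The a path compares randomised groups. The b path compares people with high and low mechanism scores within an arm, and randomisation does nothing for that comparison. Two non-causal routes can make b significant:

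- **Reverse causation.** Someone who has stopped smoking may report more confidence in abstaining because they have stopped.
- **Stable confounding.** A lasting trait may raise both the mechanism and the outcome at every visit.

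The instruments make the first route plausible. The smoking status questionnaire is listed both as a primary outcome and as a mechanism measure, and the fruit and vegetable staging measure includes current intake. The article does not say that either will be used as a mediator.

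Aim 2 is one of two specific aims, and the proportion mediated will be reported. A consequence of behaviour change could be presented as the way MAPS works.

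**Working it through.** **1. The plan's own figure.** The article gives no figure for mediation. Table 1 (Power, Continuous outcomes) anchors the inputs: 160 per arm, three follow-ups, two-sided 0.05, ESS = 480/(1 + 2×ICC). The detectable difference is (1.960 + 0.842)×√(2/ESS). At ICC 0.3, ESS = 300 and the difference is 0.229, as stated. The five rows give 0.181, 0.198, 0.229, 0.256 and 0.313, against a stated 0.314 in the last.

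**2. Assumed scenario.** MAPS raises the outcome by 0.3 SD at each follow-up (0.3 is the average difference used in the Power section). The outcome drives the same-visit mechanism with correlation c, and the mechanism has no effect on the outcome. Assumptions not in the article: c = 0.2 to 0.5, and the same-visit pairing. ICC is 0.1 to 0.5, within the range of Table 1.

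**3. Expected result.** Then b = c, a = 0.3c, and the proportion mediated is a×b/0.3 = c². The mechanism's ICC is c²×ICC. At c = 0.3 and ICC 0.3:
- VIF = 1 + 2×0.09×0.3 = 1.054 and ESS = 480/1.054 = 455.4.
- SE(a) = √(2/455.4) = 0.0663 and z = 0.09/0.0663 = 1.36.
- P(a significant) = 27%.

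Since b is practically always significant, 27% is also the rate of false mediation.

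**4. Simulation** (500 trials per scenario, categorical time, participant-clustered standard errors, unadjusted 0.05). The b path was significant in 100% of trials for every c shown.

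| c | Rule falsely met, same visit, treatment-only b | Median proportion mediated |
|---|---|---|
| 0.2 | 16–17% | about 4% |
| 0.3 | 26–30% | about 9% |
| 0.5 | 56–62% | about 25% |

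If MAPS also moves the mechanism directly by 0.3 SD (c = 0.3, ICC 0.3), a = 0.39. The rule is then met in 100% of trials, with a median proportion mediated of about 40%. If treatment changes neither variable, the rule is met in about 5%.

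**5. Previous-visit mechanism instead.** With treatment-only adjustment, reverse causation gives b = c×ICC, from 0.2×0.1 = 0.02 to 0.5×0.5 = 0.25. The b path is significant in 8–100% of trials. Lagging alone does not rescue the rule. With adjustment for the prior outcome and both baseline values, b is significant in 4–7% and the rule is met in 0.6–4% (about 5% when MAPS also moves the mechanism directly).

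**6. What baseline adjustment does.** It does not remove reverse causation: the same-visit rule is still met in 15–62%. It does reduce bias from a stable trait. If the trait carries half the variance of both variables, b = 0.5/(0.5 + 0.5) = 0.50 without adjustment. Given baseline mechanism and outcome, the trait's variance falls to 1/(1/0.5 + 2/0.5) = 1/6, and b = (1/6)/(1/6 + 1/2) = 0.25. Simulation gave a fall from 0.50 to 0.18–0.25. A b of that size can still be significant, so the gain is in bias, not in the frequency of declaration.

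**7. What the lagged model costs.** With true same-visit mediation (treatment to mechanism 0.3 SD, mechanism to outcome 0.4, ICC 0.3–0.5; assumptions), the same-visit model detects it in 86–96% of trials and the lagged, adjusted model in 5–6%. In a further simulation, adding baseline values to the same-visit model left a true b unbiased and raised power from 89–94% to 99%.

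**The case against.** The strongest reply is that a condensed article need not list visit pairing and covariates for a mediation model. Controlling for treatment is simply how the product method is defined, and the cited source or the full protocol may supply the rest. This stands for the pairing. A reader might infer that a same-visit regression is planned, but the article neither states nor excludes one, and four visits would allow a lag. It does not dispose of the rest. The article states when mediation will be declared and names treatment as the adjustment, and step 5 shows that this is inadequate under either pairing.

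A reader might also infer that reverse causation will be reported as mediation in any effective trial. That is too strong. The rule also needs a significant a path, and the false rate runs from about 16% to 100% on assumed inputs. The simulations use a continuous outcome and unadjusted tests, whereas smoking is binary and a Westfall-Young adjustment is planned where appropriate, so the percentages are illustrative.

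Third, a reader might want the lagged model to replace the same-visit one. The document's own theory argues against this: it describes motivation as fluctuating from moment to moment and changing rapidly, which fits a six-month lag poorly. Step 7 shows the price. The choice between models is a trade-off, not a correction.

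**Conclusion.** The point holds. The stated b path adjusts for intervention condition only and fixes no order between mechanism and outcome, so stable confounding or reverse causation can be reported as mediation. With same-visit pairing, a 0.3 SD treatment effect on the outcome, c of 0.2 to 0.5, and a mechanism with no effect on the outcome, the rule is met in about 16% to 100% of trials. The top figure belongs to the case in which MAPS moves the mechanism directly, which is what it is designed to do. All these rates rest on assumed inputs; none is a prediction for this trial. The consequence is confined to Aim 2: the randomised comparisons of Aim 1, the sample size and the power are untouched. It is worth settling before analysis, because the baseline values are already planned.

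**What to change.** 1. Add the baseline mechanism and baseline outcome to both the a and b paths. All participants smoke at entry, so for smoking use baseline cigarettes per day, which is already a minimisation factor. This reduces but does not eliminate confounding, improves precision and needs no new data.
2. State which visit's mechanism is paired with which visit's outcome.
3. Add a sensitivity analysis in which the mechanism at the previous visit predicts the outcome at the next (6 to 12 and 12 to 18 months), adjusted for the earlier outcome and the baseline values.
4. Describe same-visit results, including the proportion mediated, as associations consistent with mediation unless the lagged analysis supports the direction.

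The cost is analysis wording and one extra model. The lagged model uses two visit pairs instead of three and has very low power if mechanisms act within a visit interval. It should not be the sole basis for a claim, and a null result from it should not be read as absence of mediation. It also addresses direction rather than stable confounding: in the trait example of step 6, conditioning on the earlier outcome as well leaves a trait variance of 1/(2 + 3×2) = 0.125 and b = 0.125/(0.125 + 0.5) = 0.20. A positive lagged result therefore still needs cautious wording.
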